## Version History

| Version: | Version Date: | Changes:                                                                                                             |
|----------|---------------|----------------------------------------------------------------------------------------------------------------------|
| 0.1      | 23/7/22       | Original version                                                                                                     |
| 0.2      | 13/11/22      | Update variable list                                                                                                 |
| 0.3      | 21/11/22      | Update background & variable list                                                                                    |
| 0.4      | 13/12/22      | Update variable list. Add provisional priority grouping of risk factors. Update statistical analysis text.           |
| 0.5      | 15/1/23       | Update variable list, clarify outcome and index ACCT definitions.                                                    |
| 0.6      | 30/1/23       | Add one variable to variable list                                                                                    |
| 0.7      | 22/5/23       | Clarification of diagnosis risk factors and outcome definitions                                                      |
| 1.0      | 19/6/23       | Set as v1.0                                                                                                          |
| 1.1      | 28/6/23       | Amendment to timepoint for definition of diagnosis risk factor                                                       |
| 1.2      | 4/7/23        | Removal of self-harm during ACCT risk factor as a result of amendment of definition; clarify length of ACCT variable |

## Study Summary

**Design:** Retrospective multi-centre cohort study.

**Participants:** Male and female prisoners, aged 18+, in selected category A-C prisons in England who have been managed by the Assessment, Care in Custody and Teamwork (ACCT) process in response to concerns of being at risk for self-harm or suicide.

**Data sources:** Three linked data sources: ACCT records, SystmOne medical records and Nomis (a central prison database).

**Study period:** Included participants had ACCTs closed prior to June 2022, with a minimum of three months of follow-up per participant.

**Risk factors:** A range of variables including demographics characteristics, variables indicative of mental health at opening and closure of the ACCT, history of self-harm, variables relating to history of and reasons for incarceration, variables indicative of health status and medication use.

**Primary outcome:** ACCT reopening within 3 months following closure of the ACCT. The target sample size was 750, anticipating that a 20% event rate would yield 150 outcome events within 3 months.

**Outputs:** The main objective is to produce models that estimate outcome probabilities within 3 months, with appropriate measures of predictive accuracy.

These models will be used to obtain scoring systems for the calculation of risk to be used prospectively at the time of ACCT closure.

## **1. Study background**

Rates of self-harm in prisoners are high in absolute and relative terms. In 2021, there were 54,027 reported incidents of self-harm in 11,292 prisoners, a rate of 688 per 1,000 prisoners. This has increased from the period of 2011-2017, where the annual rate was below 500 per 1,000 prisoners. Over the same period, there were more than 2,400 hospital attendances as a result of self-harm incidents, a rate substantially higher than in community-based persons. Self-harm is the strongest risk factor for suicide in custody and on release, which are both elevated compared to population controls.

The ACCT process (Assessment, Care in Custody and Teamwork) was introduced to improve risk management process (Prison Service Instruction 64/2011). Previous NIHR-funded research showed that 28% of prisoners self-harmed in the 6 months following closure of the ACCT document (Horton, 2014; Horton 2018). This research concluded that a particular evidence gap was the lack of a structured approach for the assessment of risk of recurrent self-harm on ACCT closure, and that existing tools and models were not adequate. Their research also highlighted the potential importance of novel modifiable risk factors, that if studied in larger samples, could inform identification of needs, assessment and risk management.

A particular problem identified was the lack of a structured approach for the assessment of risk of recurrent self-harm on ACCT closure. This research is necessary to improve the process by which risk can be assessed and stratified after an episode of self-harm. Current clinical practice in England and Wales, and also internationally, lacks reliable and valid structured approaches to stratify risk of recurrent self-harm, link higher risk prisoners to appropriate care pathways, and more efficiently allocate limited resources.

This Statistical Analysis Plan relates to a retrospective cohort study for the development of a risk assessment tool for self-harm within three months in prisoners at the point of ACCT closure. The wider project contains further substudies: a qualitative investigation into acceptability of the risk prediction tool to relevant stakeholders, and a prospective validation study of the performance of the risk prediction tool in an external validation sample.

## 2. Statistical Analysis

Available variables, and the data sources used to collect them, are listed in Appendix 1.

The main statistical analysis method used will be Cox proportional hazards regression for survival analysis, using time to first ACCT reopening following the closure of the index ACCT as the primary outcome and a set of pre-specified candidate predictors (see separate subsection below) as covariates. In the event that the goodness-of-fit of the Cox model is inadequate, other more suitable survival analysis models, including parametric survival models, will be explored.

We will further extend the basic model to allow for possible time-varying effects of risk factors (Thomas and Reyes, 2014, Section 2.3) and/or to allow dynamic prediction using time-varying covariates (Van Houwelingen and Putter, 2012) using the 'dynpred' R package, to allow the risk to be re-estimated at the time of post-ACCT review (which occurs 7 days after closure in older ACCTs and 6 weeks after closure in newer ACCTs). This may require refitting of the model to incorporate data that is available at a second baseline (the post-ACCT review) that was unavailable at the first baseline (closure of the original ACCT).

The primary outcome is self-harm and/or substantially elevated risk or concern of future self harm that leads to a new ACCT being opened, within 3 months following ACCT closure, among prisoners who remained in custody at the time of data collection. Model fitting will be performed using follow-up data within 3 months of follow-up. Risk estimates will use the 3-month event horizon and model performance measures will be calculated in relation to this time point. Risk estimates will also be expressed conditional on the length of the post-ACCT period that has already elapsed, to allow for the likely non-linear decline in risk over time, the initial 30 days after ACCT closure being a particular high-risk period for self-harm. The distribution of risk estimates observed will guide a decision about a probability threshold indicative of high risk, although performance at a range of thresholds will be presented.

Individuals for whom no outcome event has occurred at the time of last follow-up will be considered as right-censored at that time. This includes those who have left prison, for whom the release date is recorded.

Each individual has an 'index ACCT' that defines the time point at which risk factor variables are available, and the closure of this ACCT is interpreted as time 0 for defining subsequent follow-up times. In the case that more than one ACCT from the same individual is available as an index ACCT, the most recent of these that has substantially complete risk factor data will be used in the primary analysis. A sensitivity analysis will be carried out to check that the selection of this index ACCT does not have an undue influence on results.

Covariates that have more than 30% missing data will be excluded. Missing data on covariates with at most 30% missing data will be imputed via multiple imputation (with twenty imputations) using a regression model that uses other risk factors and the outcome variables as explanatory variables (Sterne et al., 2009). Estimates of coefficients in the final prediction rule will be combined across imputations, using standard methodology (Barnard and Rubin, 1999). It is possible that the variable selection procedure would give different sets of variables in different imputations of the data-set; for this reason, the 'RR' method described by Wood et al. (2008) will be used. In this method,

summary estimates are computed by combining information across all imputed data-sets at each stage as part of a single variable selection process.

Internal validation will be assessed using bootstrapping to assess the predictive accuracy of the model (Harrell et al., 1996). Predictive accuracy will be summarised using several summary measures, including the concordance index (Harrell et al., 1982) and estimates of sensitivity and specificity corresponding to different values of a risk threshold. The proportions of predicted and observed events at different levels of predicted probability will be compared using a calibration plot.

Data will be collected from multiple prison sites (expected to be 6 different prisons in England). The main model will be fitted using data from all sites combined. Performance measures will also be presented stratified by site in order to identify whether there are any major between-site differences that may impact on performance in an external validation sample.

This analysis plan does not incorporate an external validation step as it is planned to conduct a separate external validation substudy, using data from a different selection of prisons, concurrently with the analysis in the model development stage.

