| Drug screen                                         | Nomis    | 2 | Binary                    | At start of custody.
Categorised as Yes (positive) or No (no test recorded).                                                                             |
| Index offence                                       | Nomis    | 2 | Binary                    | Categorised as 'Violent' or 'Non-violent' index offence                                                                                                     |
| Number of transfers in current prison term          | Nomis    | 2 | Discrete or categorical   |                                                                                                                                                             |
| Time until expected release                         | Nomis    | 2 | Continuous                | Calculated as time between ACCT closure date and expected release date. If included in model, must be used alongside life sentence and IPP variables below. |
| Life sentence                                       | Nomis    | 2 | Binary                    | Categorised as Yes or No                                                                                                                                    |
| IPP (imprisonment for public protection) sentence   | Nomis    | 2 | Binary                    | Also includes other non-life sentences for which an expected release date is not applicable. Categorised as Yes or No.                                      |
| First time in custody                               | Nomis    | 2 | Binary                    | Categorised as Yes or No                                                                                                                                    |
| Time since first reception in custody               | Nomis    | 2 | Continuous or categorical |                                                                                                                                                             |
| IDTS/DARS referral                                  | Nomis    | 2 | Binary                    | Integrated Drug Treatment System or Drug and Alcohol Rehabilitation Services referral. Categorised as Yes or No.                                            |

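### The primary outcome is restricted to prisoners still in custody at data collection, which contradicts the rule that censors released prisoners at release and selects on status known only after time 0

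*SAP*

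**What the plan says.** The primary-outcome paragraph of SAP section 2 counts new ACCTs "within 3 months following ACCT closure, among prisoners who remained in custody at the time of data collection".

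The following paragraph gives the censoring rule: "Individuals for whom no outcome event has occurred at the time of last follow-up will be considered as right-censored at that time". It then adds: "This includes those who have left prison, for whom the release date is recorded".

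Elsewhere:

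- The Study Summary states the primary outcome as reopening within 3 months, with no custody restriction. Under study period it describes closures before June 2022 "with a minimum of three months of follow-up per participant".
- Section 2 fixes the time origin: "the closure of this ACCT is interpreted as time 0 for defining subsequent follow-up times".
- The Study Summary says the scoring systems are "to be used prospectively at the time of ACCT closure".
- On size, the Study Summary says: "The target sample size was 750, anticipating that a 20% event rate would yield 150 outcome events within 3 months".
- Appendix 1 lists time until expected release as a Group 2 candidate predictor.

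**The concern.** A prisoner released before the data were collected is outside the cohort under the first rule and inside it, as a censored or event observation, under the second. Two analysts following the SAP could build different primary datasets.

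The two rules also differ in kind. Custody at data collection is settled after time 0, and possibly long after the 3-month horizon. A score used at ACCT closure is applied to people whose later custody status is unknown, so a model fitted only to those who stayed does not describe the people it will score. The planned bootstrap validation, calibration plot and site-stratified performance would not show this, because they all use the same selected sample.

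**Working it through.** **1. The plan's own figure.** 750 × 0.20 = 150 events, as stated. No number in the SAP is disputed; what is unclear is who makes up the 750.

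**2. The two rules applied to the same people.** These are illustrative individuals, with data collected after the release in each case.

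| Person | Custody restriction | Censoring paragraph |
|---|---|---|
| ACCT reopened on day 20, released on day 60 | Excluded; an observed event is lost | Kept, event on day 20 |
| No reopening, released on day 60 | Excluded | Kept, censored on day 60 |
| No reopening, released at month 5, data collected at month 8 | Excluded; a complete 3-month outcome is lost | Kept, event-free to 3 months |

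If data collection is at least 3 months after every closure, the restriction removes essentially everyone released within the horizon. Section 2 fits the model only to follow-up within 3 months, so releases after that do not matter for censoring. The release-censoring rule is then left with almost nothing to act on.

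**3. Loss of people and events.** The SAP gives no release rate, so the release fractions r are assumptions. Take 750 people at closure, constant and independent hazards, and a 20% risk of reopening by 3 months in the absence of release:

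- h = −ln(0.8)/3 and g = −ln(1 − r)/3 per month
- kept and censored: events = 750 × h/(h + g) × [1 − exp(−3(h + g))]
- restricted to those in custody at 3 months (the earliest collection time): people = 750 × (1 − r), events = 20% of these

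For r = 20%, g equals h, so the first formula gives 750 × 0.5 × (1 − 0.8 × 0.8) = 750 × 0.18 = 135.

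| Released by 3 months (assumed) | Events, kept and censored | People, restricted | Events, restricted |
|---|---|---|---|
| 10% | 143 | 675 | 135 |
| 20% | 135 | 600 | 120 |
| 30% | 127 | 525 | 105 |
| 40% | 119 | 450 | 90 |

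**4. Effect on absolute risk, released people at higher hazard.** Let r be the fraction released before data collection and HR their hazard relative to those retained, both assumed. With h now the cumulative hazard over 3 months in those retained, solve

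(1 − r)(1 − e^(−h)) + r(1 − e^(−HR·h)) = 0.20.

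The risk seen in the retained cohort is 1 − e^(−h):

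- r = 0.2, HR = 1.25: 19.2%
- r = 0.3, HR = 1.5: 17.7%
- r = 0.5, HR = 2: 14.0%. Here, with x = e^(−h), 0.5x + 0.5x² = 0.80 gives x = 0.860.

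**5. Effect in both directions.** Assume half the cohort has a mean time to release of 4 months and half 24 months, with an overall 3-month risk of 20%. Data collection at 3, 6 and 12 months retains about 68%, 50% and 33% of the cohort.

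| Hazard of reopening, short-stay against long-stay | Risk in retained, collection at 3 / 6 / 12 months |
|---|---|
| Half | 22% / 23% / 25% |
| Equal | 20% / 20% / 20% |
| Double | 18% / 17% / 15% |

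Check of the first cell: at 3 months the short-stay group makes up 0.349 of those retained, and the group risks are 14.0% and 26.0%, so 0.349 × 14.0% + 0.651 × 26.0% = 21.8%.

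**The case against.** The strongest defence is that the restriction was never meant literally. The Study Summary states participants and outcome without it, and a rule for released prisoners would be almost pointless if they had been excluded. On this view the phrase says only, and loosely, that an ACCT can be reopened and observed only in custody. That meaning would fit the censoring paragraph. It does not fit the wording, which ties custody to the time of data collection and not to follow-up. What stands is that the SAP does not establish which cohort will actually be built. What does not stand is that the text can be left as it is.

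Several stronger inferences are tempting but not supported:

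- **The three-month minimum as a second selection on the future.** It appears under study period, beside the closure cut-off, and reads naturally as a calendar window. It conflicts with the censoring rule only if it means observed follow-up per person.
- **Risk will be underestimated.** That follows only if released prisoners have the higher hazard. With the opposite assumption the retained risk is too high, and with equal hazards it is unchanged.
- **Time until expected release will have almost no short values.** The predictor is "Calculated as time between ACCT closure date and expected release date", and expected release is not actual release. The literal rule would thin the short end; how far is unknown.
- **Self-inflicted deaths should count as events.** The SAP consistently defines the outcome by ACCT reopening, and Appendix 1 lists no date or cause of death. Counting deaths would change the endpoint and would not resolve this contradiction.

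It is also fair to object that a wording change is cheap only if the released prisoners' records can be obtained, which the SAP does not show.

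**Conclusion.** Wrong as written. The contradiction lies within SAP section 2 and is certain. One of the two rules, followed literally, selects on status after time 0 for a score intended for use at time 0.

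The consequence for absolute risk is not certain. The range of roughly 14% to 25% for a true 20% rests wholly on assumed release fractions, release times and hazard ratios. It shows what could happen and does not estimate what will. There is no bias in absolute risk if release is unrelated to risk.

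The loss of people and events from the closure cohort does not depend on that relation: it occurs whenever anyone is released before data collection. The event counts above assume that the 750 are counted at closure. If the 750 are those left after the restriction, 150 events may still be reached, but the excluded people are still missing from the population the score is for.

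**What to change.** In SAP section 2:

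1. Delete the custody restriction that ends the primary-outcome sentence.
2. Define the cohort as all eligible prisoners in custody at index ACCT closure.
3. Keep prisoners released within 3 months, with follow-up ending at the recorded release date, as the censoring paragraph already states.

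In the Study Summary, state that the three-month minimum means at least three months between index closure and the data cut, not three months of observed follow-up for each person.

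**Cost.** The change is mainly wording. Some people will have less than 3 months of follow-up, so 750 participants may yield somewhat fewer than 150 observed events: about 143 to 119 if 10% to 40% are released by 3 months, under the assumptions above. If released prisoners were not sampled, their linked ACCT, SystmOne and Nomis records must be added. If that is not possible, the restriction should be reported as a limitation on the population to which the score applies.

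### With release right-censored, the Cox 3-month probability is a risk assuming continued custody; the SAP does not say so, and does not settle whether released prisoners are in the cohort

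*SAP*

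**What the plan says.** The Study Summary sets the aim: "The main objective is to produce models that estimate outcome probabilities within 3 months, with appropriate measures of predictive accuracy". The models are to become scores for prospective use when an ACCT is closed. It also gives the planning figures, "The target sample size was 750, anticipating that a 20% event rate would yield 150 outcome events within 3 months", and describes the cohort as followed "with a minimum of three months of follow-up per participant".

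Section 2. Statistical Analysis states the method: "The main statistical analysis method used will be Cox proportional hazards regression for survival analysis", with time to first reopening after closure of the index ACCT as the outcome. On censoring it says: "Individuals for whom no outcome event has occurred at the time of last follow-up will be considered as right-censored at that time". It then adds: "This includes those who have left prison, for whom the release date is recorded". The same section defines the primary outcome "among prisoners who remained in custody at the time of data collection". It bases the choice of a high-risk threshold on the distribution of the risk estimates.

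In Appendix 1, time until expected release is a Group 2 candidate predictor: "Calculated as time between ACCT closure date and expected release date". Under the selection rule in the Risk factors subsection, Group 2 variables may be dropped. The SAP does not mention competing events, cumulative incidence, or a risk conditional on staying in custody.

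**The concern.** ACCT is a custodial process. The SAP does not say that a reopening is impossible after release, but it describes no ACCT outcome outside prison, so the inference is direct. Release therefore does more than hide a later event: it prevents one. If it is handled as ordinary censoring, the model's 3-month risk answers the question of what would happen if the person stayed inside for the full period. A user given an outcome probability within 3 months may take it as the chance that this prisoner's ACCT will be reopened. The two differ most for people close to release, and absolute risks and a threshold on them are the product of the study.

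Nothing planned closes the gap. If time until expected release is kept in the model, it changes the reopening hazard, but the prediction still runs to 3 months as if custody continued. Calibration against a Kaplan-Meier type of observed risk would target the same continued-custody quantity and could not show the difference.

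A second problem sits beside the first. If the outcome applies only to people still in custody at data collection, the cohort is selected on something that staff cannot know at ACCT closure.

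**Working it through.** **Inputs.** From the SAP: 750 participants, 20% with the event by 3 months, 150 events (Study Summary); one Cox model with release censored, and the first 30 days described as a high-risk period (2. Statistical Analysis). Assumed, because the SAP does not give them: 3 months taken as 90 days; a constant release hazard; and *r*, the probability of release by day 90 in the absence of a reopening, over a range.

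**The plan's figure.** 750 × 0.20 = 150, as stated. There is no power calculation to reproduce.

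**Direction.** Let h(t) be the reopening hazard, S(t) the survival from a model that censors release, and R(t) the probability of not yet being released.
- Risk from the censored model: 1 − S(90) = ∫ h(t) S(t) dt.
- Probability of reopening before release: CIF = ∫ h(t) S(t) R(t) dt.

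Since R(t) ≤ 1, the CIF cannot exceed 1 − S(90). The two are equal only if nobody is released while still at risk within the window.

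**Cohort average, constant hazards.** Hold the censored estimate at 20%. Then λ = −ln(0.8)/90, μ = −ln(1 − r)/90, and CIF = λ/(λ + μ) × (1 − exp(−90(λ + μ))).

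For r = 10%: 90λ = 0.2231, 90μ = 0.1054, and the CIF is (0.2231/0.3285) × (1 − 0.8 × 0.9) = 0.679 × 0.28 = 0.190.

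| Assumed r | Censored estimate | CIF | Gap (points) | Ratio | Expected reopenings in 750 |
|---|---|---|---|---|---|
| 0% | 20.0% | 20.0% | 0 | 1.00 | 150.0 |
| 5% | 20.0% | 19.5% | 0.49 | 1.025 | 146.4 |
| 10% | 20.0% | 19.0% | 0.98 | 1.052 | 142.6 |
| 20% | 20.0% | 18.0% | 2.00 | 1.111 | 135.0 |
| 30% | 20.0% | 16.9% | 3.07 | 1.181 | 127.0 |

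For scale, the binomial standard error of 20% in 750 is √(0.2 × 0.8/750) = 1.46 points. The gaps at 5, 10, 20 and 30% are therefore 0.33, 0.67, 1.37 and 2.10 standard errors.

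**Front-loaded reopening hazard.** If half of the 90-day cumulative hazard falls in the first 30 days (assumed), the CIF at r = 10, 20 and 30% is 19.2, 18.3 and 17.4%. The gap is somewhat smaller.

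**A person with a known release day.** For a stated risk of 20% and release on day t, the risk before release is 1 − exp(−H(t)), with H(90) = −ln(0.8) = 0.2231.
- Day 14: constant hazard, 1 − exp(−0.2231 × 14/90) = 3.4%; front-loaded, 1 − exp(−0.2231 × 0.5 × 14/30) = 5.1%.
- Day 30: 7.2% constant; 10.6% front-loaded.

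**The SAP's statements side by side.** One sentence in section 2 provides for people who have left prison and censors them at release. Another confines the outcome to people still in custody at data collection. The Study Summary gives everyone at least three months of follow-up. Taken literally, the last two leave no releases in the 3-month window, and the censoring sentence then has nobody to act on within it. All three cannot describe the same cohort.

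**The case against.** The strongest reply is that the custody wording in the outcome definition points to risk while in custody as the target. For that target, censoring at release is acceptable if release is independent of reopening risk given the covariates, and nothing is overstated. This stands as far as it goes: it is a legitimate target. But the SAP never labels its output that way, and the wording refers to custody at data collection, not through the 3 months.

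A second reply is that, read literally, the cohort contains no releases within 3 months, so the gap in the data is zero. This also has force, and it is why an unconditional claim that the tool overstates risk would go too far. It does not rescue the plan, because that reading replaces a censoring question with selection on a later status.

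Third, cumulative incidence may serve the purpose less well. The background section describes a tool for self-harm risk and notes that suicide risk is raised on release too. A high-hazard prisoner due out in two weeks would score low only because a reopening could no longer be recorded. This is a good reason not to replace the Cox score outright. It is no reason to leave its meaning unstated.

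Fourth, a reader might infer that external validation will find fewer reopenings than predicted, varying with turnover between prisons. The SAP leaves validation to a separate substudy whose methods are not shown. A shortfall would appear if release were counted as a competing event or raw proportions were used, and need not appear if release were censored there too. It is possible, not certain.

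**Conclusion.** The point holds as a mismatch between what is estimated and what it is called, together with a contradiction over who is in the cohort. With release censored, the Cox output is a 3-month risk given continued custody, and even that reading needs release to be independent of reopening risk given the model's covariates. Taken as the actual probability of reopening, it is too high wherever releases occur in the window.

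The average size rests on a release share that the SAP does not give: about half a point to one point on 20% at 5 to 10% released, two to three points at 20 to 30%, and zero with no releases. For one person with a known early release the difference can be large (20% against 3.4 to 5.1% for day 14). That contrast assumes an average hazard and a fixed date, and the SAP does not show how many such people there are.

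A reader might conclude that the Cox model is wrong or that the tool certainly overstates risk. The SAP supports neither. The model is a valid cause-specific model for reopening, and whether its risk is too high depends on the target and on how many people are released. Both need to be stated.

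**What to change.** 1. Reconcile the outcome population with the censoring sentence: include all prisoners with an eligible ACCT closure, whatever their later custody status. Restate the three-month minimum to fit, for example as a closure date at least three months before data collection.
2. State the target of the 3-month probability. If the score stays on the single Cox model, label it *risk if the person stays in custody for the full 3 months*.
3. Report the number released within 3 months without a reopening.
4. Beside the Cox risk, report the 3-month cumulative incidence of reopening with release as a competing event, from cause-specific Cox models for reopening and for release. Time until expected release and the life and IPP indicators are natural covariates for the release model. Estimate the observed risk by Aalen-Johansen, and calibrate each estimate against its own target.

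The cost is SAP wording and one extra model on release dates already recorded. The reopening coefficients from the cause-specific Cox model need not change. The drawbacks are a second, lower set of absolute risks to explain, a second baseline hazard, and a release model that may transport less well between prisons than the reopening model.
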